# Comparative study of the efficacy and safety of minimally invasive interlaminar full-endoscopic discectomy versus conventional microscopic discectomy in single-level lumbar herniated intervertebral disc (ENDO-F Trial): a multicenter, prospective, randomized controlled trial protocol

**DOI:** 10.1186/s13018-022-03052-1

**Published:** 2022-03-28

**Keywords:** Conventional microscopic discectomy, Interlaminar full-endoscopic discectomy, Lumbar disc herniation, Study protocol, Minimally invasive surgery

## Abstract

**Background:**

Advances in minimally invasive surgery have expanded the indications for interlaminar full-endoscopic discectomy. Although the clinical outcomes for this approach may be equivalent to those of conventional microscopic discectomy, the supporting evidence is still based on small, single-center, prospective, and retrospective studies. Therefore, a multicenter randomized controlled trial is warranted.

**Methods:**

This will be a prospective, multicenter, randomized controlled trial comparing the efficacy and safety of interlaminar full-endoscopic discectomy to those of conventional microscopic discectomy. The trial will enroll 100 participants with a lumbar disc herniation, 50 in each group. The primary outcome will be the Oswestry Disability Index (ODI) score at 12 months post-surgery. Secondary outcomes will be back and leg pain (visual analog scale); the ODI; the EuroQol-5-dimension score; patient satisfaction; and walking distance/time and time to return to daily activities post-surgery. Surgical outcomes will include postoperative drainage, operative time, duration of hospital stay, postoperative creatine kinase level as an indicator of muscle injury, and postoperative scarring. Postoperative magnetic resonance imaging, computed tomography, and simple radiography will be performed to evaluate radiographic outcomes between the two surgical approaches. Surgery-related complications and adverse effects will be evaluated as safety outcomes. A single assessor at each participating hospital, blinded to group allocation, will assess the enrolled participants at baseline, at 2 weeks, and at 3, 6, and 12 months postoperatively.

**Discussion:**

This trial is designed to determine whether interlaminar full-endoscopic discectomy is clinically comparable to microscopic discectomy to treat lumbar disc herniations. All efforts will be made to reduce bias, including adequate sample size, blinded analyses, and multicenter prospective registration. The outcomes will inform practice, providing the evidence needed for using interlaminar full-endoscopic over microscopic discectomy by confirming the potential of this technique to improve patient satisfaction and clinical outcomes.

*Trial registration*: Clinical Research Information Service; cris.nih.go.kr. (KCT0006277); protocol version (v1, June 8, 2021).

## Background

Discectomy is the most common surgical method for resolving lumbar radiculopathy caused by disc herniation and nerve root compression [1, 2]. Currently, microscopic discectomy is performed as minimally invasive surgery, reducing the invasiveness of conventional open discectomy [3–5]. Minimally invasive spinal surgery has been developed by using a tubular retractor, microscope, and endoscope to achieve effective neural decompression while preserving the stabilizing structures of the spine [4–7]. Although technically more demanding, interlaminar full-endoscopic discectomy has significantly reduced surgical invasiveness, thereby expanding the indications for endoscopic surgery [5, 8–10]. Specifically, interlaminar full-endoscopic discectomy offers several advantages over conventional microscopic discectomy, including a smaller skin incision and, thus, less scarring and less muscle damage, a lower infection rate and volume of blood loss, a less painful recovery, and a shorter hospital stay [3, 11–17]. Previous studies have reported no differences in clinical outcomes between interlaminar endoscopic and microscopic discectomy [18–22]. However, the evidence regarding the efficacy and safety of interlaminar full-endoscopic discectomy compared with those of microscopic discectomy is limited by the small sample size in these studies and type of research design, namely retrospective, single-center prospective designs [7, 18–25]. Therefore, a multicenter, randomized controlled trial (RCT) is warranted.

To address this gap in evidence, we propose a multicenter, prospective RCT to compare the outcomes of interlaminar full-endoscopic discectomy versus those of microscopic discectomy. Our guiding hypothesis is that the efficacy and safety of interlaminar full-endoscopic discectomy and microscopic discectomy of the lumbar spine will be similar.

In addition to the findings from previous studies, if this non-inferiority RCT with a high evidence level shows no differences in the primary outcomes of neural decompression between the two discectomy surgeries, these results, combined with less invasiveness of interlaminar full-endoscopic discectomy may suggest that interlaminar full-endoscopic discectomy is a superior alternative to conventional open surgery.

## Methods/design

### Trial design

This study aims to evaluate the non-inferiority of the outcomes of interlaminar full-endoscopic discectomy versus those of microscopic discectomy using a multicenter RCT design. Our methods have been approved by the institutional review boards of the participating hospitals (The Catholic University of Korea Seoul St Mary’s Hospital; Kyung Hee University Medical Center; Chungdam Wooridul Spine Hospital; Wiltse Memorial Hospital; Seoul National University Bundang Hospital; Kangnam Sacred Heart Hospital; and The Catholic University of Korea Daejeon St. Mary’s Hospital).

### Study group

The study sample will be 100 adults, 20–80 years of age, who present with radiating pain in the lower extremities due to a lumbar disc herniation. The method for sample size calculation is provided below. Fifty participants will be allocated each to the interlaminar full-endoscopic group and microscopic discectomy group. The equivalence between the two groups at baseline will be ascertained. Participants will be recruited from the five participating hospitals.

### Inclusion criteria

The inclusion criteria are as follows: patients for whom conservative treatment has failed and who are considered suitable for decompression surgery; age, 20–80 years; diagnosis of single-level lumbar disc herniation; radiating pain to the lower extremities, with a pain score > 4 on a 10-point visual analog scale (VAS); lumbar disc herniation cases wherein both interlaminar full-endoscopic discectomy and conventional microscopic discectomy are considered possible and appropriate by an operator; ability to follow instructions and to provide consent for participation; and willingness to comply with the trial’s follow-up protocol. The following types of disc herniation will be included: protruded, extruded, and migrated types of disc herniation in the central canal and subarticular zones [26].

### Exclusion criteria

The exclusion criteria are as follows: the presence of a spondylolisthesis (Meyerding grade ≥ II); spinal stenosis of more than a moderate degree (Schizas classification grade ≥ B) [27]; history of lumbar spinal surgery at the same level, including recurrent disc herniation; the presence of degenerative lumbar scoliosis (Cobb angle > 20°); other spinal diseases (e.g., ankylosing spondylitis, spine tumor, fracture, or neurologic disorders); and “any other” patient characteristic or disorders that the surgeons consider inappropriate for participation, including extreme sensitivity to pain, myofascial pain syndrome, history of paresis, and severe knee joint osteoarthritis. Patients with a sequestrated disc herniation and those with foraminal and extraforaminal disc herniation will be excluded [26].

### Recruitment

This will be a multicenter RCT and will include patients who decide to proceed with a one-level discectomy for lumbar disc herniation at each of the five participating hospitals between June 2021 and December 2024. There will be no recruitment via social media. The study researchers from each of the five participating hospitals will screen potential participants to determine their eligibility and willingness to participate.

### Data collection

After providing informed consent, participants will be enrolled in the study and will undergo baseline assessments, including the following: magnetic resonance images (MRIs), simple radiographs, the Oswestry Disability Index (ODI) score, the EuroQol-5-dimension-5-level (EQ-5D-5L) questionnaire, and the 10-point pain VAS scale, and demographics and baseline patient characteristics [including age, gender, occupation, comorbidity (diabetes mellitus, hypertension), bone mineral density, body mass index, medical/surgical history, smoking/drinking habits, physical examination, and laboratory test]. The assessor will be blinded to participants’ personal information.

### Randomization and follow-up

After completing the baseline assessments, participants will be block-randomized into either the control (microscopy) or intervention (endoscopy) group, using a 1:1 allocation ratio, with a block size of four. The randomization list will be computer-generated and integrated into a web-based electronic case report form (eCRF) platform (iCReaT; internet-based clinical research and trial, icreat.nih.go.kr). The central randomization will be conducted by a contract research organization company (Helptrial), and the data will be accessible only to the trial’s authorized researchers. The randomization of patients to either the control or intervention group will be presented to the study surgeons in each participating hospital using consecutively numbered opaque envelopes.

To evaluate the primary and secondary outcomes, follow-up assessments will be planned for each participant at 2 weeks and at 3, 6, and 12 months after surgery. An independent researcher will perform the assessments at each time-point of follow-up. Phone interviews will be used under unavoidable circumstances where in-person follow-up is not possible (Fig. 1).

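### The protocol names no hospital stratum for randomisation and no hospital term in the primary comparison, and it counts five participating hospitals in two sections but lists seven in another

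*Protocol article*

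**What the plan says.** **Allocation (Randomization and follow-up).** "participants will be block-randomized into either the control (microscopy) or intervention (endoscopy) group, using a 1:1 allocation ratio, with a block size of four". The section continues: "The randomization list will be computer-generated and integrated into a web-based electronic case report form (eCRF) platform". It also states: "The central randomization will be conducted by a contract research organization company". Allocations are then "presented to the study surgeons in each participating hospital using consecutively numbered opaque envelopes". No stratification factor is named. The section does not say whether there is one sequence for the whole trial or one per hospital.

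**Analysis (Statistical analyses).** The 12-month ODI score is compared between the two groups, and the 95% confidence interval is set against 12.8 points. No hospital term is mentioned. Clinical and radiographic outcomes outside the repeated-measures model are compared by t-test or chi-square test.

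**Hospitals.** Study group: "Participants will be recruited from the five participating hospitals". Recruitment: "The study researchers from each of the five participating hospitals will screen potential participants", and the same section gives five once more. Trial design: "Our methods have been approved by the institutional review boards of the participating hospitals". The list attached to that sentence has seven names. Five of them are "Kyung Hee University Medical Center; Chungdam Wooridul Spine Hospital; Wiltse Memorial Hospital; Seoul National University Bundang Hospital; Kangnam Sacred Heart Hospital", with one more before and one after.

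**The concern.** Hospital is a natural source of variation in this trial. Surgeons are specific to a hospital, one assessor per hospital rates all outcomes (Blinding), and the Background section describes the endoscopic technique as harder to perform. Blocks filled by patients from several hospitals keep the overall totals equal but do not balance the arms within any one hospital. With about 20 patients per hospital (100/5) or 14 to 15 (100/7), chance can leave a hospital well off 1:1. Its surgeons, assessor and local habits are then partly mixed up with the technique.

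The outcomes most exposed are operative time, duration of hospitalisation and satisfaction. The first two bear on the argument in the Background section that endoscopy is less invasive.

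The conflicting hospital count is a separate reporting error. It does not cause imbalance, but a reader cannot tell which hospitals enrol or over how many the 100 patients are spread.

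**Working it through.** **The plan's own figure.** The protocol gives no figure for balance within hospital. Its only relevant number is 100 patients, 50 per arm. With a margin of 12.8, SD 17.1, 90% power and 20% loss, two one-sided tests at 0.05 need 40 evaluable patients per arm, and 40/0.80 = 50. A non-inferiority test at one-sided 0.05 gives 39 to 40 per arm after the same inflation. That difference is a separate matter; 100 is taken as given here.

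**Assumptions, because the documents give no recruitment by hospital.** Patients arrive from the hospitals in random order. Sizes are 5 equal (20 each), 7 equal (two of 15, five of 14), 5 unequal (40/25/15/12/8) or 7 unequal (35/20/15/10/8/7/5). The first calculations suppose one list shared by all hospitals.

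**Step 1. Imbalance in one hospital.** Under random arrival, the number allocated to endoscopy in a hospital of size s is hypergeometric (50 of 100, s drawn). The arm difference D then has variance s(100 − s)/99.

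- For s = 20: 20 × 80/99 = 16.2, an SD of 4.0 patients. The mean absolute difference is about 3.1.
- The chance that a given hospital of 20 ends 14:6 or worse is about 8%.

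**Step 2. At least one hospital at 70:30 or worse.** Simulation of one shared list in blocks of four, 20,000 runs per scenario, compared with blocks of four within each hospital:

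| Hospitals | Shared list | Blocked within hospital |
|---|---|---|
| 5 equal | 31% | 0% |
| 7 equal | 60% | 0% |
| 5 unequal | 42% | 0% |
| 7 unequal | 85% | 0% |

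As a check on the first row, five times 8% bounds it at about 40%. The 85% partly reflects very small hospitals: in a hospital of five, a 4:1 split already counts. Blocked within hospital, the arm difference in any hospital is at most 2 patients.

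**Step 3. Effect on the unadjusted ODI difference.** With 50 per arm, the root-mean-square chance shift is (SD of hospital means) × √(ΣVar(D))/50.

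- 5 equal: √(5 × 16.16)/50 = √80.8/50 = 0.18.
- 7 equal: (2 × 15 × 85 + 5 × 14 × 86)/99 = 86.6, and √86.6/50 = 0.19.
- Between-hospital SD of 5 (assumed): 5 × 0.18 = 0.9 points. SD of 8 (assumed): 8 × 0.18 = 1.4 points.

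For comparison, the margin is 12.8. The standard error of the difference with 40 evaluable per arm is 17.1 × √(2/40) = 3.8.

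**Step 4. What adjustment alone recovers.** With K hospitals on a shared list, a hospital-adjusted comparison keeps on average 1 − (K − 1)/99 of the information of perfect balance.

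- K = 5: 1 − 4/99 = 96%.
- K = 7: 1 − 6/99 = 94%.

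The simulation agrees (94% to 96% on average, 88% to 91% at the 5th percentile). Blocking within hospital gives 99% to 100%.

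**Step 5. Predictability of a fixed block of four within a hospital.** There are six arrangements of two and two. Once three allocations in a block are known, the fourth is certain. In two of the six arrangements the first two are alike, so in 1/3 of blocks the third is certain as well.

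**The case against.** The strongest objection is that the missing stratum is read from silence. The article never calls the list unstratified or shared, and numbered envelopes at each hospital could well be separate sequences, in which case no hospital is more than two patients out. A condensed article may also leave strata to the full protocol. This stands as far as it goes: a reader might infer that randomisation is definitely unstratified, and the text does not establish that. But the section already gives method, ratio, block size, platform, central conduct and delivery for a single list. Its plain reading is one list, and the analysis section names no hospital term that would suggest otherwise.

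Other stronger readings also fail:

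- *That the trial result would be biased.* The imbalance is random, so the comparison is not biased on average, and the typical ODI shift is small against the margin.
- *That later adjustment helps little.* It keeps 94% to 96% of the information on average. Only a nearly one-armed hospital would contribute little, and 70:30 is not that.
- *That a known share of the 17.1-point SD is hospital variation.* The protocol takes the SD from cited work, one of whose two sources it groups with retrospective and single-centre studies. It does not show that the SD contains any between-hospital part.
- *That five versus seven breaks the randomisation.* An unstratified list does not depend on the number of hospitals.
- *That balance by surgeon is known to fail.* Surgeons per hospital are not given, so this cannot be computed.

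A last objection concerns the remedy. Surgeons know the allocations, and eligibility rests partly on the operator's judgement (Inclusion criteria). Fixed blocks of four within a hospital would therefore expose upcoming allocations and could exchange random noise for selection bias. This stands, and the fix must deal with it.

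**Conclusion.** The point holds as a gap in design and reporting that should be closed. It does not threaten the validity of the trial. The protocol names no hospital stratum and no hospital term in the primary comparison. If the list is shared, a split of 70:30 or worse in at least one hospital has a chance of about 31% (five equal hospitals) to 60% (seven equal), and 42% to 85% under the assumed unequal recruitment.

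The cost is precision: 4% to 6% of the information in an adjusted analysis, or a typical shift of 0.9 to 1.4 ODI points in an unadjusted one if hospital means have an SD of 5 to 8. Outcomes driven by local practice plausibly suffer more, but the documents give no figures from which to size that. All of this rests on one shared list, random arrival order and assumed hospital sizes.

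The contradiction between five and seven participating hospitals is certain, needs no assumption, and must be reconciled in any case.

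**What to change.** 1. Give one list of enrolling hospitals and make Trial design, Study group and Recruitment agree with it. If some hospitals gave ethics approval but do not enrol, say so.
2. State whether the list is blocked within hospital. If it is not, stratify the central randomisation by hospital, for the remaining patients if recruitment has started. Replace the published fixed block of four with varied block sizes that are not disclosed to the hospitals.
3. In either case, include hospital as a factor in the primary ODI comparison.

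The cost is a setting in the existing central system, a wording correction and K − 1 degrees of freedom (4 with five hospitals, 6 with seven). Incomplete blocks may leave the overall totals slightly off 50:50. The imbalance within a hospital can reach half the largest block, so a block larger than four would loosen the two-patient limit a little. Balance by surgeon is still not guaranteed. The sample size stays at 100.

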### Blinding

All the primary and secondary outcomes will be assessed at each participating hospital by a single assessor, who will be blinded to group allocation. The patients themselves who are assessors of the patient-reported outcomes (the VAS score of back and leg pain, EQ-5D-5L score, and ODI score) are blinded (i.e., they are not informed of their assignment). The investigators of the patient-reported outcomes are also blinded.

Because blinding of patients is an integral part of this study, the research personnel and healthcare providers will not disclose surgical information to patients throughout the study. However, blinding may fail due to other available information such as operative time, size of the skin incision, and hospital cost. Therefore, patients will be asked to guess the surgery they underwent, and the extent of successful blinding will be assessed based on this parameter.

Postoperative surgical scarring, the extent of disc removed, and the presence/absence of injury to the facet joint on postoperative MRI or computed tomography (CT) images will be measured by a blinded assessor. Complications observed on simple radiographs, adverse events and the severity of these events, as well as surgery-related events, will be evaluated and managed by a blinded assessor. Surgeons will be made aware of the procedure performed (interlaminar full-endoscopic discectomy or microscopic discectomy) in each case. This information will not be revealed by either the participants or surgeons to the assessor. If unblinding is required, the assessor will be required to submit a justification to the trial team based on the assessment findings.

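### A fixed, published block size of four, with envelopes given to unblinded surgeons who influence eligibility, could make up to one third of allocations predictable with certainty if blocks run within hospital

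*Protocol article*

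**What the plan says.** The section Randomization and follow-up of the protocol article sets allocation "using a 1:1 allocation ratio, with a block size of four". On the list itself it says: "The randomization list will be computer-generated and integrated into a web-based electronic case report form (eCRF) platform". On who runs it: "The central randomization will be conducted by a contract research organization company". It then says that the allocation "will be presented to the study surgeons in each participating hospital using consecutively numbered opaque envelopes".

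Three other sections bear on the point:

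- **Blinding:** "Surgeons will be made aware of the procedure performed" in each case, so past allocations are known to those who operate.
- **Inclusion criteria:** a patient qualifies only if both operations "are considered possible and appropriate by an operator".
- **Exclusion criteria:** there is an open category for any further characteristic or disorder "that the surgeons consider inappropriate for participation".

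The Recruitment section gives screening to study researchers at each hospital. Randomization follows the baseline assessments. The article does not say whether blocks are formed within hospital, or how many surgeons operate at each one.

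**The concern.** Permuted blocks of one known size let an observer count. Once one arm has used its two places in a block of four, the rest of that block is determined. The observer who matters is someone who both knows past allocations and can influence who enters next. Here the surgeon fits both descriptions. The block size is in print while recruitment runs, and consecutively numbered envelopes at a hospital are a convenient way to follow a sequence.

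A surgeon who expects a particular arm could judge a borderline patient unsuitable, or bring eligible patients forward in a different order, before randomization. The evaluation schedule leaves room for this: eligibility is checked at a screening visit up to four weeks before surgery, and randomization belongs to the surgical visit. Selection of this kind cannot be reliably corrected in analysis. It would bear on a single comparison of 12-month ODI in 100 patients.

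**Working it through.** The article gives no predictability figure, so there is none to reproduce.

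**Inputs from the article.** Block size 4 and ratio 1:1 (Randomization and follow-up). 100 participants (Sample size justification). Five recruiting hospitals (Study group; Recruitment), although Trial design lists seven for ethics approval, so both numbers are tried.

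**Assumptions, not in the article.** The observer knows the position within the block. The number of surgeons per hospital is varied from one to three. Patients fall at random across hospitals or surgeons.

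**1. Upper bound: every earlier allocation in the block is seen.** There are six equally likely sequences. AABB and BBAA each leave 2 certain allocations, and the other four leave 1 each:

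(2×2 + 4×1)/6 = 1.333 per block; 1.333/4 = 33.3%.

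The chance of guessing right, by position, is 1/2, 2/3, 2/3 and 1:

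(1/2 + 2/3 + 2/3 + 1)/4 = 17/24 = 70.8%, against 50% by chance.

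Allowing for incomplete last blocks in hospital-level lists, simulation gives about 31% certain (five hospitals) or 30% (seven).

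**2. Only part of the block is seen.** Suppose each earlier allocation was seen with probability 1/m.

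- Third place: certain if both earlier ones were seen and were the same arm, 1/m² × 1/3.
- Fourth place: certain if all three were seen, 1/m³; or if exactly two were seen and were the same arm, 3 × (1/m²)(1 − 1/m) × 1/3. These add to 1/m².

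The sum is 4/(3m²) per block, or 1/(3m²) per allocation.

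| Situation | m | Formula | Simulation |
|---|---|---|---|
| Hospital lists, one informed surgeon | 1 | 33.3% | 30-31% |
| Hospital lists, two surgeons, own cases only | 2 | 8.3% | about 8% |
| Hospital lists, three surgeons, own cases only | 3 | 3.7% | about 3% |
| One list across five hospitals, own hospital only | 5 | 1.3% | 1.3% |
| One list across seven hospitals, own hospital only | 7 | 0.7% | 0.7% |

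The simulated hospital-list figures are slightly lower because last blocks are incomplete. For one list across five hospitals the best-guess rate is about 54%.

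**3. Effect of varying the block size.** Simulation of hospital-level lists of 20, with all earlier allocations seen and the set of sizes known but not their order:

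| Block sizes | Certain | Best guess |
|---|---|---|
| 4 only | 33% | 71% |
| 4, 6 | 5.7% | 69% |
| 2, 4, 6 | 3.8% | 70% |
| 4, 6, 8 | 2.4% | 67% |

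**4. Terminal imbalance.** The worst case is half of the last block in one arm: 4/2 = 2 with blocks of four, 8/2 = 4 when a block of eight can occur.

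**The case against.** The strongest reply is that the article describes central randomization by a contract research organization from a computer-generated list. If that is one list across hospitals, a surgeon who sees only local cases can be certain of about 1% of allocations, and the fixed block size hardly matters. This stands, and it is why one third can only be called an upper bound.

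Existing safeguards also count. Study researchers screen, consent and enrolment precede the baseline assessments, and randomization follows them. What remains open is anticipation before a patient is enrolled, which is narrower than free choice after the arm is seen. It is not closed, because the surgeons' opinion is written into both sets of criteria.

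A reader might infer three stronger things that the article does not support:

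- **That a third of allocations are in fact predictable.** This needs blocks within hospital and a surgeon informed of every local allocation. Neither is stated.
- **That web randomization and envelopes contradict each other.** They can be one chain: a list held centrally, with each assignment conveyed in an opaque envelope, which is a recognized way to conceal allocation.
- **That the trial lacks stratification by hospital and risks lopsided hospitals.** A condensed article may simply leave stratification out, so its silence is no error. The argument also needs one list across hospitals, whereas the one-third figure needs hospital-level blocks, so the two cannot both apply.

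**Conclusion.** The point holds as a conditional weakness in concealment. The text establishes a single block size of four, its publication during recruitment, envelopes to surgeons at each hospital, surgeons' knowledge of earlier operations, and their say in eligibility. The size depends on facts that the article does not give: up to 33% of allocations certain (best guess 71%) with hospital-level blocks and a fully informed surgeon, about 3-8% with two or three surgeons who each know only their own cases, and about 1% with one list across hospitals. Numbered envelopes at each hospital make the first situation plausible without showing it.

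Nothing here shows that selection has occurred. The change is still worth making, because it is cheap and the bias could not be reliably removed afterwards.

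**What to change.** For patients not yet randomized, replace the fixed block of four with randomly varying block sizes, for example 4, 6 and 8, known only to the contract research organization and not published while recruitment continues. Release each assignment through iCReaT, and only after consent, eligibility and baseline data are recorded there, in place of envelopes held for surgeons.

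With hospital-level blocks, certain predictions fall from about 33% to about 2%. The best guess falls only from 71% to about 67%, so varying the blocks removes certainty more than it removes informed guessing; recording eligibility before release has to do the rest. If the list already runs across hospitals, there is little predictability to remove. In that case, adding hospital stratification would raise it: about 1.3% certain and a 54% best guess now, against about 2.4% and 67% for hospital-level blocks of 4, 6 and 8. The change proposed here therefore leaves the structure of the list as it is.

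The cost is a new list for the remaining patients, a short amendment to the randomization text, and a possible terminal imbalance of up to 4 patients per list instead of up to 2.
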